## Abstract

**Background:**

Spontaneous intracerebral hemorrhage is a disease with high morbidity, high disability rate, high mortality, and high economic burden. Whether patients can benefit from surgical evacuation of hematomas is still controversial, especially for those with moderate-volume hematomas in the basal ganglia. This study is designed to compare the efficacy of endoscopic surgery and conservative treatment for the moderate-volume hematoma in spontaneous basal ganglia hemorrhage.

**Methods:**

Patients meet the criteria will be randomized into the endoscopic surgery group (endoscopic surgery for hematoma evacuation and the best medical treatment) or the conservative treatment group (the best medical treatment). Patients will be followed up at 1, 3, and 6 months after initial treatment. The primary outcomes include the Extended Glasgow Outcome Scale and the Modified Rankin Scale. The secondary outcomes consist of the National Institutes of Health Stroke Scale and the mortality. The Barthel Index(BI) will also be evaluated. The sample size is 100 patients.

**Discussion:**

The ECMOH trial is a randomized controlled trial designed to evaluate if endoscopic surgery is better than conservative treatment for patients with moderate-volume hematomas in the basal ganglia.

**Trial registration:**

Chinese Clinical Trial Registry: ChiCTR-TRC-11001614

(http://www.chictr.org/en/proj/show.aspx?proj=1618)

## Background

Spontaneous intracerebral hemorrhage (SICH) is a disease with high morbidity, high disability rate, high mortality, and high economic burden [1,2]. Its annual incidence is about 20 cases per 100,000 population [3,4]. More than 70% patients end up with death or dependence [5,6].

The main clinical management of SICH includes surgical and medical treatment. Whether patients can benefit from surgery is still controversial, especially for those with basal ganglia hemorrhage, which is the major subtype of SICH [7]. Surgical evacuation of hematomas can relieve the mass effect and reduce the harmful substance released during their coagulation, liquefaction, and resolution [8-10], but surgical procedures may also injure the brain tissue, and cause other operative complications. These disadvantages reduce the benefit of surgery. Some clinical trials were carried out to compare surgery with medical treatment. The most famous trial is the STICH trial conducted by Mendelow et al. [5]. 1033 patients were randomized. After 6 months follow-up, 26% of patients in the early surgery group had a favourable outcome compared with 24% in the group of initial conservative treatment. Early surgery did not show significant advantages. However, in this study less than 25% of the operations were minimally invasive. Trials of stereotactic surgery or craniopuncture were also carried out [11-13]. But none of the trials and systematic reviews provide sufficient evidence for the choice of treatments [6,14-16].

In clinical practice, neurologists and neurosurgeons tend to choose conservative treatment for patients with small-volume hematomas, and surgery for those with large-volume hematomas [17]. However, when the volume of the hematoma exceeds 60 ml, neither of the methods give much help [18]. Treatments for moderate-volume hematomas have the most uncertainty. Some recently randomized trials indicate these patients may benefit from minimally invasive surgery [13,19]. Kim et al. [19] randomized 387 patients with basal ganglia or thalamus hematomas to stereotactic-guided evacuation (group A) or conservative treatment (group B), and the mean hematoma volume was 23.1 ml. At the end of 6 months follow-up, the mean score of modified Barthel index was 90.9 in group A and 62.4 in group B, and the mean score of modified Rankin scale was 1.2 in group A and 3.0 in group B. Patients received stereotactic-guided evacuation had better clinical outcomes and motor function.

Endoscopic surgery is one of the minimally invasive ways for hematoma evacuation. Compared with other surgical methods, it has advantages as follows. A). The hematoma evacuation is performed under direct vision of neurosurgeons. It’s much easier to spot any bleeding site, so that the risk of postoperative rebleeding is lower. B). The evacuation rate of hematomas is higher because of a wider vision. C). This also leads to less brain retraction and brain tissue injury. D). The operation time is shorter. Cho et al. [20] carried out a randomized controlled trial which compared endoscopic surgery, stereotactic aspiration and craniotomy. The results showed endoscopic surgery had the highest hematoma evacuation rate, the lowest mortality and complication rate, and shorter waiting time than stereotactic aspiration. However, there are few randomized controlled trials which contrast endoscopic surgery and conservative treatment. The trial completed by Auer et al. [21] in 1989, showed 28% lower of the mortality in the endoscopic surgery group than the medical treatment group after 6 months follow-up. But this trial did not restrict the volume of hematomas.

It's not clear whether endoscopic surgery gives this type of patients better outcomes, so we have designed this study to find more clues for the clinical management of SICH.

## Methods

### Study objective

To compare the efficacy of endoscopic surgery and conservative treatment for the moderate-volume hematoma in spontaneous basal ganglia hemorrhage.

### Inclusion criteria

· Spontaneous basal ganglia hemorrhage confirmed by computed tomography(CT).

· The volume of the hematoma is between 20 ml to 40 ml. Small intraventricular hemorrhage is not counted.

· Admission within 36 hours from the ictus.

· Age between 15 to 75 years old.

· Glasgow Coma Score(GCS) ≥ 8.

### Exclusion criteria

· Any sign of brain herniation, including deep coma, unilateral or bilateral pupil dilation, abnormal posture, or unstable vital signs.

· Hemorrhage caused by aneurysm, vascular malformations, tumor apoplexy, trauma, or cerebral infarction. Computed tomography angiography will be performed.

· Large intraventricular hematomas which occupy half of the cross section area of the lateral ventricle on CT scans, or hydrocephalus caused by hematocele.

· Primary intraventricular hemorrhage.

· Dysfunction of blood coagulation, thrombocytopenia, or history of taking any kind of drugs which affect coagulation function in the past 40 days.

· Before the ictus, the patient has severe physical or mental illness which causes significant disability, or the patient has other severe comorbidity.

· The patient is pregnant.

### Sample size

The rate of the favourable outcome of patients with basal ganglia hemorrhage is about 30% for conservative treatment [5,6] and 60% for endoscopic surgery [22-24]. A sample size of 86 will be required with a significance level of 5% (2-sided) and a power of 80%. In consideration of the loss to follow-up, the sample size is enlarged to 100.

### Randomization

The minimization method is adopted for the patients allocation, and it’s performed by a minimization software. When the qualification of a patient is confirmed, the investigator sends the basic information of the patient to a special trialist who is responsible for patients randomization. After the information of the patient is imported, the software will randomize him/her into the endoscopic surgery group or the conservative treatment group. The presetted variables for minimization are age, hematoma volume, and admission GCS.

The allocation of patients cannot be changed. If the patients' condition deteriorates during conservative treatment, and the surgical indications are clear, hematoma evacuation will be performed after fully informed consent.

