#### *Primary outcomes*

The primary outcomes of the study are the Extended Glasgow Outcome Scale (GOSE)[26] and the Modified Rankin Scale (mRS) at 6 months after initial treatment. Both scales will be measured with structured interviews.

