### Statistical analysis

Both Intention To Treat (ITT) and Per-Protocol (PP) analysis will be performed. The level of significance is 0.05, and Power is 80%. The quantitative data will be analyzed by *t*-test. Chi-square test will be used to analyze the categorical data. For the ordinal data, Wilcoxon rank test is adopted. And survival analysis will be carried out for further comparison of mortality. Logistic regression will be used to adjust the effect of multivariables.

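### Allocation is minimised on age, hematoma volume and GCS, but the test fixed for the ordinal primary scales is unadjusted; if these factors are prognostic it is conservative and gives up power relative to an adjusted analysis

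*Protocol article*

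**What the plan says.** Under Randomization, the protocol article states "The minimization method is adopted for the patients allocation, and it’s performed by a minimization software", and then "The presetted variables for minimization are age, hematoma volume, and admission GCS".

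The section on primary outcomes names two scales, GOSE and mRS, assessed at 6 months. Each is ordinal.

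The Statistical analysis section assigns tests by type of data: a t-test for quantitative data, a chi-square test for categorical data, and, for the type that covers the primary scales, "For the ordinal data, Wilcoxon rank test is adopted". None of these three uses the minimisation factors. The section also says "Logistic regression will be used to adjust the effect of multivariables". It does not name the covariates, link them to the minimisation factors, or say whether the regression or the unadjusted test is the main analysis.

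The Sample size section works with a binary favourable outcome, 30% under conservative treatment against 60% under endoscopic surgery: "A sample size of 86 will be required with a significance level of 5% (2-sided) and a power of 80" per cent. The total is then raised to 100 for loss to follow-up.

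**The concern.** Minimisation makes the two arms alike on age, volume and GCS. If these predict the 6-month outcome, the difference between arms varies less from trial to trial than under simple randomisation. An unadjusted test still uses the full outcome variance, so its p-values are too large on average and it rejects a true null less often than 5% of the time. A test that adjusts for the factors uses the smaller residual variance. It restores the nominal level and gains power from data already held at randomisation.

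With about 86 evaluable patients, this matters most if the true effect is smaller than the planned doubling of the favourable rate. That is possible: the Background section cites a surgical trial of 1033 patients with 26% against 24% favourable.

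**Working it through.** **1. The plan's own figure.** Inputs from Sample size: 30% and 60%, two-sided 5%, 80% power. With pooled variance, n per arm = 2 × 0.45 × 0.55 × (1.960 + 0.842)² / 0.30² = 43.2, about 86 in total. The formula with pooled variance under the null and separate variances under the alternative gives 42 per arm, 84 in total. Power is 81.0% at 43 per arm and 86.6% at 50 per arm. The 86 reproduces, for an unadjusted comparison of a binary outcome.

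**2. The mechanism in closed form.** Suppose balance is perfect and the factors explain a share R² of the outcome variance. The unadjusted statistic then has variance 1 − R² instead of 1, so its type I error is 2Φ(−1.96/√(1 − R²)):

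- R² 0: 5.0%
- R² 0.2: 2Φ(−2.19) = 2.8%
- R² 0.4: 2Φ(−2.53) = 1.1%

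Real minimisation balances categories, and with a random element, so actual figures should lie between these and 5%.

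**3. Simulated type I error, ordinal scale.** Assumptions, none of them in the documents: 1:1 allocation, N = 86, a seven-level outcome, three continuous factors cut into thirds for minimisation, and a biased coin of 0.8 or 0.9.

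| R² | 0 | 0.1 | 0.2 | 0.3 | 0.4 |
|---|---|---|---|---|---|
| Wilcoxon, coin 0.8 | 6.1% | 4.5% | 3.5% | 3.1% | 2.4% |
| Wilcoxon, coin 0.9 | 5.4% | 4.4% | 3.8% | 3.0% | 2.2% |

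Rank-based ANCOVA on the three factors stayed at 5.0 to 5.9% (coin 0.8) and 5.1 to 5.6% (coin 0.9). A variant with three three-level factors gave somewhat lower Wilcoxon figures, 2.7% at R² 0.2 and 1.6% at R² 0.4.

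**4. Power at 60% of the planned shift.** On the log-odds scale, 30% to 60% is −0.847 to 0.405, a shift of 1.253. Sixty per cent of it is 0.752, which takes 30% to about 48% favourable. With coin 0.9:

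| R² | 0 | 0.1 | 0.2 | 0.3 | 0.4 |
|---|---|---|---|---|---|
| Wilcoxon | 52% | 52% | 54% | 54% | 54% |
| Rank-based ANCOVA | 52% | 57% | 62% | 67% | 72% |
| Gap (points) | 0 | 5 | 8 | 13 | 18 |

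The three-level variant gave gaps of 9, 15 and 19 points at R² 0.2, 0.3 and 0.4. The closed form agrees. Power of 52% at R² 0 means a mean statistic of 1.96 + 0.05 = 2.01. At R² 0.4 the unadjusted power is Φ(0.05/0.775) = 53% and the adjusted power Φ(2.01/0.775 − 1.96) = 74%.

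**5. Power at the planned effect.** In the three-level variant the Wilcoxon test has 94 to 96% and the adjusted test 97 to 99%. The coin 0.9 runs of step 4 gave gaps of 0 to 3 points.

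**6. The binary favourable outcome.** N = 86, coin 0.8, 4,000 trials per cell (Monte Carlo error about 0.3 points for type I error and 0.6 for power). Prognostic strength is in log-odds per SD of each factor.

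| Strength | 0 | 0.4 | 0.7 | 1.0 |
|---|---|---|---|---|
| Type I error, chi-square | 5.0% | 4.5% | 3.4% | 2.9% |
| Type I error, adjusted logistic (likelihood ratio) | 5.9% | 5.8% | 5.6% | 6.0% |
| Power, 30% vs 60%, chi-square | 80.9% | 81.5% | 83.5% | 84.3% |
| Power, 30% vs 60%, adjusted logistic | 81.2% | 85.4% | 90.7% | 94.2% |

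The gap is about 0 to 10 points, a small part of which reflects the slightly liberal likelihood-ratio test. The unadjusted chi-square never falls below the stated 80%.

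**The case against.** **An adjusted analysis is already planned.** This stands. The logistic regression fits the binary favourable outcome on which the trial was sized, and a proportional-odds model is itself a form of logistic regression, so the wording does not exclude it. A reader might infer that no adjustment is planned, or that the regression is only supplementary. The article supports neither, because it leaves the regression's role open.

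**Covariate lists belong in the statistical analysis plan.** This also stands: their absence from a journal article is no finding, and a fuller document may name them. But the article does fix one thing, an unadjusted test for ordinal data, and that choice does not use the minimised design.

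**The size is assumed.** This stands too. The documents give no prognostic strength, number of levels or coin probability. Eligibility narrows two of the factors (volume 20 to 40 ml, GCS at least 8), so a high R² is not certain. With no prognostic value there is no loss, and the largest gaps arise at 60% of the planned shift, a scenario that the documents do not contain.

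**The remedy may be liberal.** This stands in part. The ordinal simulations used rank-based ANCOVA, not the proportional-odds model. A small check of the proportional-odds likelihood-ratio test (five R² values from 0 to 0.3, 1,000 null trials each) gave 5.5 to 8.2% per cell, about 6.5% pooled. That check is noisy: the unadjusted Wilcoxon also read 7.3% at R² 0. Even so, nominal error should not be taken for granted at this size.

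**Conclusion.** The point holds in a limited form. The test that the article assigns to the primary scales ignores the factors on which allocation is minimised, and the planned regression is not tied to them. If the factors are prognostic, the Wilcoxon test is conservative: type I error falls from about 5% at R² 0 to about 2 to 3% at R² 0.4. Relative to an adjusted test it gives up about 0 to 20 points of power at 60% of the planned effect and 0 to 4 points at the planned effect.

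These ranges rest on an assumed R² of 0 to 0.4, 1:1 allocation, three levels per factor, a coin of 0.8 or 0.9, and 86 evaluable patients.

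A reader might infer that the trial is underpowered, or that its p-values are certainly too large. The documents support neither. The stated 80% is met by the unadjusted analysis, any loss depends on a prognostic strength that the documents do not give, and the error is on the safe side for false positives. This is a nearly free improvement to the analysis, not a flaw that threatens validity.

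**What to change.** In the Statistical analysis section:

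- Name as the main analysis of GOSE and mRS an ordinal (proportional-odds) regression, or a rank-based ANCOVA, on treatment plus age, hematoma volume and admission GCS.
- Put the same three factors in the planned logistic regression for favourable outcome.
- Keep the unadjusted Wilcoxon and chi-square tests as sensitivity analyses.
- If a likelihood-ratio test from an adjusted model is used, add a rank-based or permutation check, because such tests can be slightly liberal at about 86 patients.

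The cost is a few sentences. All three factors are recorded for every patient at randomisation, so no new data and no change in sample size are needed. The change should be fixed before the data are unblinded. If a full analysis plan already says this, the article's wording only needs to be brought into line with it.

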### Blinding

Both patients and surgeons cannot be blinded. In order to minimize the measurement bias, the following procedures are made. A). Patient outcomes will be measured by two special investigators who are not involved in the allocation and the treatment. Before the outcome measurement starts, patients, their relatives, and the related medial staff will be told not to reveal any information about the treatment. B). Every patient will have a gauze covered on the hemorrhage side of the head to conceal the scar or baldness. C). Because the follow-up forms and the treatment forms are printed on the same set of Case Report Form (CRF), these two investigators must hand in a copy of the original score sheets to the Quality Monitoring Board (QMB), before they are allowed to get the CRF of the patient. D). The statistical analysis will be made by a statistician who doesn't participate in the implementation of the trial, and the treatment information of the groups will be blinded.

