### Follow-up

Patients will be followed up at 1, 3, and 6 months after initial treatment.

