### Data collection and management

The allocation data of patients is kept by the trialist who specializes in randomization. Neurosurgeons should fill in CRF except the follow-up forms, which must be completed by another two investigators trained for outcome assessment. Double input will be used in the data entry. The QMB and the principal investigator will check and examine the data, then the database will be locked and sent to a statistician.

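### Release of the CRF, which contains the treatment forms, to the outcome assessors is not tied to the 6-month visit, so the blinding safeguard does not secure the primary rating

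*Protocol article*

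**What the plan says.** The Blinding section accepts that neither patients nor surgeons can be blinded and lists four measures against measurement bias. Measure A gives the rating to independent people: "Patient outcomes will be measured by two special investigators who are not involved in the allocation and the treatment". Measure C deals with the paperwork. It notes that "the follow-up forms and the treatment forms are printed on the same set of Case Report Form (CRF", and requires that the assessors "must hand in a copy of the original score sheets to the Quality Monitoring Board (QMB), before they are allowed to get the CRF of" that patient.

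Three other sections bear on this:

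- Follow-up: "Patients will be followed up at 1, 3, and 6 months after initial treatment".
- Primary outcomes: the endpoints are the GOSE and "the Modified Rankin Scale (mRS) at 6 months after initial treatment". On method: "Both scales will be measured with structured interviews".
- Data collection and management: "Neurosurgeons should fill in CRF except the follow-up forms, which must be completed by another two investigators trained for outcome assessment".

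**The concern.** With patients and surgeons unblinded, independent blinded rating is the main protection for the two primary outcomes. Measure C recognises that the CRF can unblind a rater, yet it still passes the CRF to the raters once a condition is met. That condition is the lodging of score sheets, and it is not linked to the visit that supplies the primary endpoint.

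Lodging a copy fixes what has already been scored. It does nothing for a score not yet given. If an assessor receives the CRF after the month-1 or month-3 visit, that assessor may rate the month-6 GOSE and mRS knowing which arm the patient is in. Both scales are rated from an interview. A structured interview narrows the room for judgement but does not remove it. Bias introduced in this way cannot be undone at analysis.

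**Working it through.** **Reading the sections together**

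1. Who rates: two investigators outside allocation and treatment (Blinding, measure A). No other rater is named for month 6.
2. Who completes the follow-up forms: the assessors, while neurosurgeons complete the rest of the CRF (Data collection and management). The set therefore carries treatment information.
3. Where the follow-up forms are: in the same CRF set as the treatment forms (Blinding, measure C). To complete them, the assessors must at some point hold that set.
4. When they may hold it: after score sheets are lodged (Blinding, measure C). Which visit's sheets is not stated.
5. When the primary rating occurs: month 6, after visits at months 1 and 3 (Follow-up; Primary outcomes). Two of the three visits precede it.

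Two release rules fit this text:

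| Release rule | Fits the text? | Month-6 rater shielded from the treatment forms? |
|---|---|---|
| CRF released as each visit's sheets are lodged | Yes | No: up to two releases before the primary rating |
| CRF released once, after the month-6 sheets are lodged | Yes | Yes |

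Nothing in the article selects the second rule, seals or removes the treatment pages, or assigns different raters at month 6.

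**Illustration of what rating drift could do**

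The point does not depend on this calculation.

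*Inputs from the article (Sample size):* 30% favourable under conservative treatment, 60% under endoscopic surgery, two-sided 5%, 80% power, 86 patients. *Assumed:* 1:1 allocation, hence 86/2 = 43 per arm; a binary outcome; no true effect; and the drift sizes.

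First, the plan's own figure. The pooled two-proportion formula without continuity correction gives 42 per arm, 84 in total, which is within 2 of the stated 86. Power at 43 per arm is 81.0%. The figure of 43 per arm is therefore a sound base.

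Next, let the true favourable rate be 30% in both arms, with ratings in one arm drifting upward by d, so that p1 = 0.30 and p2 = 0.30 + d. With p̄ = (p1 + p2)/2,

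- s0 = √[2p̄(1 − p̄)/43]
- s1 = √[(p1(1 − p1) + p2(1 − p2))/43]
- P(reject) = Φ[(d − 1.96·s0)/s1] + Φ[(−d − 1.96·s0)/s1]

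| d (assumed) | s0 | s1 | Upper tail | Lower tail | P(reject) |
|---|---|---|---|---|---|
| 0 | 0.0988 | 0.0988 | 0.025 | 0.025 | 0.050 |
| 0.05 | 0.1010 | 0.1009 | 0.071 | 0.007 | 0.078 |
| 0.10 | 0.1029 | 0.1023 | 0.160 | 0.002 | 0.162 |
| 0.15 | 0.1044 | 0.1031 | 0.298 | <0.001 | 0.298 |

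Exact binomial enumeration gives 0.082, 0.172 and 0.317 for the three drifts, so the normal approximation does not exaggerate.

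**The case against.** The strongest objection concerns timing. A reader might infer that the assessors receive the CRF after every visit, that the safeguard therefore covers only month 1, and that every patient seen at month 1 is rated unblinded at month 6. The documents do not support that. Measure C names no visit. It refers to score sheets in the plural and to the patient's CRF in the singular, which also fits one release after month 6. Scores are first written on separate sheets, and the article does not say that they are copied into the CRF at months 1 and 3. A team that released the CRF only after month 6 would comply fully. This objection stands, and it limits the point to a route that the text leaves open.

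A second objection is that an article condenses a fuller protocol, to which such operational detail may be left. This carries less weight. The article does not pass over the procedure. It describes it specifically, and the procedure described hands the unblinding document to the raters on a condition that does not secure the primary rating.

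Third, other protections exist. The assessors are independent and have at least 20 hours of training with a qualification exam. Patients, relatives and staff are told not to disclose treatment, the head is covered, and the interviews are structured. Mortality should not be affected by rating drift. These measures reduce the risk and the likely size of any drift. They do not help an assessor who has already seen the treatment forms.

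Fourth, the false-positive figures rest on drift sizes with no basis in the documents, and on a binary test, whereas the Statistical analysis section assigns the Wilcoxon test to ordinal data. This is correct. The figures show sensitivity and are not a forecast.

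**Conclusion.** The point holds in a limited form. The blinding safeguard is not tied to the 6-month visit. As written it protects scores already lodged, and it does not prevent the assessors from learning the allocation before they rate the primary GOSE and mRS if the CRF is released at month 1 or 3. Whether that would happen cannot be told from the article, so it would be wrong to say that the plan removes assessor blinding.

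The documents give no means of sizing the bias. The rates of about 8%, 16% and 30% are conditional on assumed drifts of 5, 10 and 15 points, a binary outcome, 43 per arm and no true effect. They show only that modest drift would matter in a trial of this size. The change is worth making because it closes a gap in the main protection for both primary outcomes at almost no cost.

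**What to change.** Either of two changes closes the route.

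1. **Separate the forms (preferred).** Print the follow-up forms as their own booklet carrying only the patient number, so that assessors never handle the treatment forms. Cost: a reprint.
2. **Tie the release to month 6.** Keep the lodging step with the Quality Monitoring Board, and state in the Blinding section that no CRF is released to an assessor until that patient's month-6 score sheets are lodged. Align the Data collection and management section, so that the assessors complete the follow-up forms from the lodged sheets after that point. Cost: a sentence in each section and later transcription.

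The lodging requirement should not be struck out along with the CRF access, because it preserves a record of the scores made before the rater saw the CRF. Neither change adds visits or staff or alters care. The change should be in place before any CRF is released to an assessor at month 1 or 3, since blinding once lost cannot be restored.
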